### Participant Timeline

Enrolment for this trial began on January 6, 2018.

**Figure 1 figure1:**
[figure not shown]
A CONSORT flowchart for the trial.

### Blinding

At the beginning of the study, participants are informed that they will receive the intervention either immediately after the baseline or at the end of the trial. Meanwhile, all instructions to participants are uniform, and the authors will not know the participants’ allocation during trial.

### Ethical Procedures and Possible Harm

The research ethics board at the first author’s university approved the current study (approval #17-174). All procedures are according to the UMIN Clinical Trial Registry (R000034388) and follow the guidelines of Standard Protocol Items: Recommendation for Interventional Trials [32]. The authors anticipate the possible harm of this intervention is minimal because participants will simply receive information related to alcohol consumption. If participants experience distress and require professional assistance during the trial, the authors will refer them to appropriate treatment.

### Power Analysis

Previous studies have suggested small effect size for internet-based interventions for drinking consumption (1 drink less per week) [12]. A power analysis was conducted in R (software for statistical computing) and found that to obtain statistically significant results a total sample of 393 is necessary for 80% statistical power at *P*<.05 for significance level. One trial conducted in Japan reported a 65% dropout rate [33]. Because a high attrition rate is expected in internet-based research, the authors will collect a sample 600 of participants.

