### Procedure and Allocation

Once participants are directed to the trial website, they will first take the screening measures (ie, AUDIT), and only those who meet the eligibility criteria will be invited to formally participate in this trial. Participants who do not meet the eligibility will be directed to a webpage showing that they are not eligible to participate in the study, whereas those who meet the criteria proceed to the next section without being told the screening results. Participants will be asked to spend between 5 and 15 minutes entering their typical drinking patterns and to think about their results and alcohol-related health. After participants fully read and understand the nature of this study, and consent to participate in the trial, they will be asked to enter their email address or their account name on the crowdsourcing site to receive notifications for subsequent follow-ups. They will then provide their demographic information and complete the measures of alcohol expectancies.

This study will be a 2-armed randomized controlled trial. Participants will be randomly allocated to either the intervention group or the control group. The website created for this trial automatically allocates participants to either group using computer-generated numbers. Both groups will complete the assessment part of the intervention. Only the intervention group will receive the personalized normative feedback and psychoeducation immediately after the baseline measures. The control group is the waitlist group of participants who will be notified that they will receive the intervention at the end of the participation.

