Figure 1 shows the flow of the trial. Participants will complete the outcome measures at baseline, 1 month, 2 months, and 6 months into the study. At each follow-up, participants will be asked to enter information about their drinking patterns since their last assessment. Specifically, they will be asked about their drinking patterns during the past month at the 1-month and 2-month follow-ups and their drinking patterns over the past 4-months at the 6-months follow-up (due to the previous assessments being conducted 1 and 4 months prior respectively). At the end of the trial participation, the participants will be thoroughly debriefed about the nature of the study. Participants registered in the research marketing company will be compensated with ¥120 (equivalent to US $1) and 1000 credits. Participants on the crowdsourcing website will receive ¥1200 (equivalent to US $11) as work compensation after completing all the follow-up measures.

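### At the only dropout rate the Power Analysis cites (65%), enrolling 600 leaves 210 completers, 183 short of the 393 it requires

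*Protocol article*

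**What the plan says.** The sizing argument is one short paragraph, the Power Analysis section of the protocol article. It has four steps.

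- **Effect.** "Previous studies have suggested small effect size for internet-based interventions for drinking consumption (1 drink less per week"). No standard deviation and no standardised effect are given.
- **Requirement.** The calculation found that "a total sample of 393 is necessary for 80% statistical power" at the 5% level. Whether the test is one- or two-sided is not stated.
- **Attrition.** "One trial conducted in Japan reported a 65% dropout rate". This is the only dropout rate in the article.
- **Enrolment.** "Because a high attrition rate is expected in internet-based research, the authors will collect a sample 600 of participants". No inflation step is shown, and no dropout rate is named as the one expected in this trial.

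Elsewhere, Procedure and Allocation describes two arms without an allocation ratio and assessments at baseline and at 1, 2 and 6 months. Statistical Analyses plans intention-to-treat with multiple imputation and a linear mixed-effects model.

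**The concern.** The paragraph is built so that the dropout rate explains why 393 becomes 600. A reader will conclude that 600 enrolled should still leave about 393 with data. At the cited rate it leaves little more than half of that.

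What is at stake is how a non-significant result will be read. If 600 is taken to be protected against attrition at 80% power, a null finding at month 6 looks like fair evidence that the intervention does not work. With 210 completers the trial could easily miss the effect it was sized for.

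**Working it through.** **Inputs.** From Power Analysis: 393 in total, 80% power, 5% level, 65% dropout, 600 enrolled. Assumed here because the article does not state them: a two-sided test, 1:1 allocation, and an unadjusted comparison of two means at one visit (month 6).

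**1. Completers**

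- Completers = enrolled × (1 − dropout) = 600 × 0.35 = 210, or 105 per arm.
- Shortfall = 393 − 210 = 183.
- Enrolment that keeps 393 at 65% dropout = 393 / 0.35 = 1,122.9, so 1,123.
- Largest dropout at which 600 keeps 393 = 1 − 393/600 = 34.5%, about half the cited rate.

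This step needs no effect size and no assumption about the test.

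**2. What effect does 393 correspond to?**

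For two equal arms, n per arm = 2 × (1.960 + 0.842)² / d².

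- With d = 0.2, the conventional small effect, n = 2 × 7.85 / 0.04 ≈ 393 **per arm**, or 786 in total. The stated figure is therefore reproduced as a per-arm number but not as a total.
- If 393 really is the total, d = 2 × 2.802 / √393 = 0.283. For a difference of 1 drink per week this means a standard deviation of about 1/0.283 = 3.5 drinks, a value the article does not give.

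The article does not settle which reading applies, so both are carried forward.

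**3. Power**

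Power ≈ Φ(d × √(n per arm / 2) − 1.960). A t-test calculation agrees to within half a percentage point.

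| Number with data | d = 0.283 (393 is a total) | d = 0.2 (393 is per arm) |
|---|---|---|
| 600 (no dropout) | 93% | 69% |
| 393 | 80% | 51% |
| 390 (35% dropout from 600) | 80% | 50–51% |
| 210 (65% dropout from 600) | 53% | 30% |

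For 210 completers, √(105/2) = 7.246.

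- With d = 0.283: 0.283 × 7.246 − 1.960 = 0.09, so power is about 53%.
- With d = 0.2: 0.2 × 7.246 − 1.960 = −0.51, so power is about 30%.

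**4. Detectable effect at 80% power**

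- 210 completers: d = 2.802 / 7.246 = 0.387 (0.388 by t-test), about 0.39.
- 390 completers: d = 2.802 / √(195/2) = 0.284.

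**5. Where might 600 come from?**

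393 / 0.65 = 604.6. This is near 600 and is what results if 65% is treated as the share retained. The article shows no such division, so this is only a possible explanation. Steps 1 to 4 do not depend on it.

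**The case against.** Four points can be made for the plan.

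**65% is an example and not the planning rate.** This is correct: the section reports it from one other trial and then speaks only of high attrition. It would be too strong to say that the plan assumes 65%, or that it expressly claims 80% power for 600 at that rate. But no other rate is offered, and 600 works only at about half the one cited. If the authors expected about 35%, the text does not say so.

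**Completers at month 6 are not the whole analysis.** The mixed model uses baseline, month 1 and month 2 data as well, and this objection has weight. As an illustration, assume that the baseline value is adjusted for and correlates 0.5 with the outcome (not in the article). Dividing d by √(1 − 0.5²) raises power with 105 per arm to about 38% for d = 0.2 and 65% for d = 0.283. At an assumed 0.7 the figures are about 52% and 81–82%. So 80% can be reached, but only with the larger effect and a strong correlation together. Multiple imputation does not by itself restore information that was never collected. The Power Analysis counts on no such gain.

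**The trial is called a pilot, and dropout is acknowledged.** Purpose of This Study and the Discussion overview use the word pilot, and Limitations warns about substantial dropout. The stated aim is still efficacy with 80% power, and neither remark corrects the number.

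**A reader might infer that attrition alone takes power from 80% to 30%.** The article does not support that. Measured from 393 as a true total, attrition lowers power from 80% to about 53%. The 30% also needs d = 0.2, under which 393 in total gives only 51% before anyone drops out. That further loss belongs to the question whether 393 is a total or a per-arm number.

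**Conclusion.** The point holds. The one dropout rate that the Power Analysis offers does not support 600: it leaves 210 completers where 393 are required. This rests only on the article's own figures.

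The size of the power loss is conditional. It is about 53% if 393 is truly a total and about 30% if the small effect is 0.2. Both figures are for an unadjusted, two-sided, month-6 comparison with equal arms, and the planned model could do better by an amount the article does not quantify. The documents do not establish that 65% was adopted as the planning rate or that dropout was mistaken for retention.

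**What to change.** Restate the Power Analysis section without changing enrolment:

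- Name the dropout rate used for planning, and the effect size with its standard deviation. Say whether 393 is a total or a per-arm number.
- For 600 enrolled, give two scenarios side by side. At about 35% dropout: 390 completers, detectable effect about 0.28. At 65%: 210 completers, detectable effect about 0.39. Add the power for the chosen effect size from the table above.
- Do not present 600 as keeping 80% power at the cited rate. If the mixed model is expected to recover power, state the assumed correlations and the gain.
- State that a non-significant result will be reported as an estimate with its confidence interval and not as evidence of no effect.

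The cost is a few sentences and a less favourable stated power. No more participants and no change of analysis model are needed for this point.

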### Data Monitoring, Auditing, and Management

Since the intervention is a single session immediately subsequent to the baseline, the authors have determined that monitoring of participants’ reporting or interim analyses to continue or discontinue with the trial is not necessary. The authors do not plan to ask a third-party to audit the trial. All consent forms and private or identifying information will be separated during data analyses to protect anonymity.

### Statistical Analyses

To evaluate the feasibility of the website intervention, the authors will review participants’ comments about the intervention. Additionally, the authors will calculate the attrition rate from the enrollment to the final assessment. All data analysis will be performed in R [34]. First, descriptive statistics will be calculated to show the mean and standard deviation of measured variables. Data will be screened for missingness, outliers, linearity, normality, and homoscedasticity. Appropriate data transformation will be used for subsequent data analyses. Intention-to-treat analyses will be conducted to examine the efficacy of the intervention on all outcome measures. Missing data will be replaced with multiple imputations.

Linear mixed-effect model analyses of variance (ANOVA) will be used to examine the main effects of condition, the main effects of time, and the interaction effects between condition and time of the intervention on outcome measures. To examine the moderating variables between the intervention and outcome measures, alcohol expectancies and levels of AUDIT will be separately added into the model. Interactions of alcohol expectancies or AUDIT with condition, time, and condition × time (multiplying the two) will be analyzed. An R package called “nlme” will be used for these analyses [35].

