## Discussion

### Overview

The purpose of this study is to conduct a single-blind 2-armed pilot randomized controlled trial to examine the efficacy of the website intervention for 6 months for reducing alcohol consumption among Japanese problem drinkers. This study will collect data using two different crowdsourcing websites and one research marketing company. Instructions are given uniformly throughout the trial, and thus the authors will not know the allocation of the participants. Data collection is expected to end in late 2018. The authors hypothesize that the intervention will have significant effects with a medium or small effect size consistent with a similar previous study [18-20]. The effect size will likely decrease over time but may last up to 6 months, since the literature shows that the effects of computer-delivered interventions do not last for longer than 6 months [12,13,36]. The authors hypothesize that alcohol expectancies will moderate the effects of the intervention on the outcome measures. Additionally, the authors expect that the levels of the AUDIT scores will moderate the effects of the intervention on the outcomes. Participants at the harmful and hazardous level of the AUDIT score will show larger effects from the intervention than those at the dependent level. These individuals with the dependent level will require more extended internet or face-to-face interventions.

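### As written, the mixed-model ANOVA appears to count baseline as an outcome time, which shrinks the condition main effect to three quarters and uses baseline drinking inefficiently

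*Protocol article*

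**What the plan says.** Under Statistical Analyses, the protocol article commits to a linear mixed-effect ANOVA in nlme. The effects it will examine are the "main effects of condition, the main effects of time, and the interaction effects between condition and time of the intervention on outcome measures". No baseline covariate is named, the coding of time is not given, and the three effects are listed side by side without saying which one decides efficacy.

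Under Procedure and Allocation: "Participants will complete the outcome measures at baseline, 1 month, 2 months, and 6 months into the study". The same section places treatment after the first of these measurements: "Only the intervention group will receive the personalized normative feedback and psychoeducation immediately after the baseline measures".

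The Discussion (Overview) expects a fading effect: "The effect size will likely decrease over time but may last up to 6 months". The Power Analysis assumes a "small effect size for internet-based interventions for drinking consumption (1 drink less per week") and states that "a total sample of 393 is necessary for 80% statistical power". It gives no SD, standardised effect or within-person correlation.

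**The concern.** Read together, these sections most naturally describe a 2 x 4 condition-by-time model in which baseline is one of the four times. Baseline precedes treatment, so randomisation makes the expected arm difference there zero. A condition main effect averaged over all four times mixes that known zero into the treatment effect.

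The interaction does capture treatment, but it measures change from baseline. That subtracts the whole baseline difference, when only the part predicted by the correlation should be removed. Baseline drinking is already collected, so the lost precision could be recovered at no cost. The planned moderator terms that interact with condition alone would carry the same pre-treatment zero.

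At stake is power to detect an effect that the authors themselves expect to be small, in a trial for which they anticipate high attrition.

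**Working it through.** **The plan's own figure.** With two-sided alpha 0.05 and 80% power, (1.960 + 0.842)² = 7.849.
- At d = 0.2: 2 x 7.849 / 0.04 = 392.4, so 393 *per arm*.
- As a *total*, 393 fits a 1-df test at f² = 0.02: 7.849 / 0.02 = 392.4. For two equal arms this means d = sqrt(2 x 7.849 / 196.5) = 0.283.

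The article does not settle which was meant, so both values of d are carried forward.

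**Assumptions that are not in the documents.** Equal arms, unit SD, compound symmetry with correlation ρ of 0.3 to 0.7, complete data, time as a 4-level factor, and normal or chi-square approximations. With 393 in total, n = 196.5 per arm and n/2 = 98.25.

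**Dilution.** Let the follow-up effects be a, b and c. The four-time mean is (0 + a + b + c)/4, which is 3/4 of (a + b + c)/3 for any pattern of decay. With 0.2 at each follow-up it is 0.15. With 0.20, 0.15 and 0.10 it is 0.1125 against a mean of 0.15.

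**Formulas.**
- Condition main effect: variance factor (1 + 3ρ)/4, SE = sqrt(2 x factor / n).
- Baseline-adjusted average: variance factor (1 − ρ)(1 + 3ρ)/3, same SE formula.
- Both 3-df tests: noncentrality λ = (n/2) x [Σδ² − k(Σδ)²] / (1 − ρ). For the interaction k = 1/4; for the baseline-adjusted joint test k = ρ/(1 + 3ρ).

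For 0 ≤ ρ < 1, ρ/(1 + 3ρ) is below 1/4. With the same 3 df, the adjusted joint test therefore never has a smaller λ than the interaction under this covariance.

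**Worked case: d = 0.2 at each follow-up, ρ = 0.5.**
- Main effect: SE = sqrt(2 x 0.625 / 196.5) = 0.0798; 0.15 / 0.0798 = 1.88; power 47%.
- Interaction: λ = 98.25 x (0.12 − 0.25 x 0.36) / 0.5 = 5.90; power 51%.
- Adjusted joint test: λ = 98.25 x (0.12 − 0.2 x 0.36) / 0.5 = 9.43; power 73%.
- Adjusted average: SE = sqrt(2 x 0.4167 / 196.5) = 0.0651; 0.2 / 0.0651 = 3.07; power 87%.

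| Effect at 1, 2, 6 months | N | ρ | Main effect | Interaction, 3 df | Adjusted joint, 3 df | Adjusted average, 1 df |
|---|---|---|---|---|---|---|
| 0.2, 0.2, 0.2 | 393 | 0.3 | 58% | 38% | 70% | 85% |
| 0.2, 0.2, 0.2 | 393 | 0.5 | 47% | 51% | 73% | 87% |
| 0.2, 0.2, 0.2 | 393 | 0.7 | 39% | 75% | 86% | 95% |
| 0.283 at each | 393 | 0.5 | 76% | 83% | 97% | 99% |
| 0.2, 0.2, 0.2 | 210 | 0.5 | 28% | 29% | 44% | 61% |
| 0.3, 0.15, 0 | 393 | 0.5 | 29% | 85% | 90% | 63% |

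The 210 is 600 x (1 − 0.65), using the dropout rate cited in the Power Analysis.

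In the last row Σδ² = 0.1125 and (Σδ)² = 0.2025. This gives λ = 98.25 x (0.1125 − 0.0506) / 0.5 = 12.16 for the interaction and 98.25 x (0.1125 − 0.0405) / 0.5 = 14.15 for the adjusted joint test.

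**Other codings.**
- Only the three follow-ups are levels of time, with no covariate: the main effect is undiluted, with variance factor (1 + 2ρ)/3. At d = 0.2 and N = 393, power is 68% at ρ = 0.5 and 60% at ρ = 0.7, still below the adjusted average.
- Baseline is the reference level in reference-cell coding: the condition term is the baseline difference alone and carries no treatment effect.

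**The case against.** Four objections have force.

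1. **The premise is inferred.** The article does not say that baseline is a level of time or that time is a factor. The interaction would have 1 df with continuous time and 2 df with follow-ups only. This stands, and the point is worded accordingly. The other codings of the condition term above still waste the baseline or miss the treatment effect.

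2. **The model is valid.** A reader might infer that the planned analysis is biased or has the wrong error rate. It is not, and does not. Baseline as a response with a condition-by-time term gives unbiased differences in change, and estimates at each visit can be drawn from the same fit. The diluted main effect is a different and less useful estimand. Detailed contrasts may sit in an analysis plan that is not shown, so their absence is not the point.

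3. **No effect is named as decisive.** A reader might infer that efficacy rests on the omnibus interaction, or that a time main effect would count as evidence of efficacy. The text supports neither; it only lists the three effects.

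4. **A single averaged contrast is not always better.** The Discussion allows the effect to fade by 6 months. If it falls to zero (0.3, 0.15, 0), the planned interaction has about 85% power and the adjusted average 63%. This stands against making the average compulsory. It does not count against baseline adjustment, since the adjusted joint test reaches 90% in the same case.

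The power figures also depend on an assumed d. At 0.283 the planned tests come close to or exceed 80% (76% and 83% at ρ = 0.5).

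**Conclusion.** The point holds as a should-fix. On the natural reading, the condition main effect recovers exactly 3/4 of the mean follow-up effect; that fraction needs only equal weighting and a zero expected baseline difference.

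The loss of power is conditional on the stated assumptions. At d = 0.2 and N = 393, neither treatment-related test on the list reaches 80% for a constant effect at any correlation tried, whereas the adjusted average does throughout. At d = 0.283 and ρ = 0.5 the deficit is small, though the ordering is unchanged.

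The firm conclusion is that adjusting for baseline improves on the planned interaction at the same 3 df, whether the effect is constant or fades. The documents do not support calling the analysis invalid, or claiming that one particular adjusted test is best for every time course.

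**What to change.** Keep nlme and the planned data. Fit the 1-, 2- and 6-month values as outcomes with condition, visit, condition x visit, baseline and baseline x visit. Base efficacy on the baseline-adjusted condition effect over follow-up, not on a main effect that averages in baseline. Report the adjusted difference with its confidence interval at each visit.

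State in advance which test decides: the 1-df average, one named visit, or the joint 3-df test. That is the sponsor's choice. The average is stronger if the effect persists, and the joint test is stronger if it fades by 6 months.

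The cost is a change of analysis wording, with the same measurements and software. The one real trade-off is the choice of deciding test.

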### Personalized Normative Feedback

Many interventions that have shown the efficacy to reduce alcohol consumption include personalized normative feedback [17,18]. In personalized normative feedback, after users enter information about their demographics and alcohol consumption, they can compare their levels of drinking with the average levels of their age and sex.

Personalized normative feedback thus corrects users’ misperceptions of their level of drinking. Internet-based brief interventions with personalized normative feedback have been shown to reduce harmful alcohol use among Canadians [18], indigenous people in New Zealand [19], and Swiss young men [20]. Although effect sizes of these studies are between small and medium [18-20], a meta-analysis supports that personalized normative feedback is effective in reducing alcohol consumption [21].

Because both personalized normative feedback and psychoeducation involve cognitive restructuring regarding drinking patterns, further studies are needed to identify cognitive variables which can increase or decrease the effectiveness of the interventions. Alcohol expectancies are one variable to theoretically explain one’s drinking behavior. According to social learning theory, alcohol expectancies are individual beliefs about the effects of drinking on mood and behavior [22]. Alcohol expectancies are associated with frequency and quantity of alcohol consumption [23]. However, the current literature is limited in demonstrating whether the effectiveness of brief internet interventions differs according to the levels of alcohol expectancies.

In Japan, one study found that a psychoeducational video in a classroom setting increased knowledge of alcohol-related problems, but it did not reduce the number of alcohol-related problems among Japanese students in junior college at the 2-month follow up [24]. Although research in computer-delivered interventions has existed for about 20 years, very few computer-delivered interventions for reducing alcohol consumption exist in Japan. To our knowledge no prior studies have examined the effects of internet-delivered interventions using personal normative feedback among Japanese adults with problem drinking.

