### Purpose of This Study

The first purpose of this study is to examine the efficacy of the Web-based intervention on reducing alcohol consumption among Japanese adults with problem drinking by conducting a pilot trial. To better understand the effects of the intervention, this study will also explore moderators between the intervention and outcome variables such as the degree of alcohol-related problems and participants’ beliefs about the effects of alcohol consumption (ie, alcohol expectancies). The authors hypothesize that a Web-based intervention will reduce the quantity and frequency of alcohol consumption among Japanese problem drinkers. Additionally, the authors hypothesize that variables such as alcohol-related problems and alcohol expectancies will moderate the effects of the intervention on outcome measures for alcohol consumption. The reduction of alcohol consumption will be greater among individuals with harmful and hazardous levels of drinking than those at the dependent level of drinking. A brief intervention will likely not suffice for individuals with a dependent level of drinking. Moreover, stronger negative or weaker positive beliefs about the effects of drinking will reduce participants’ alcohol consumption, due to participants’ belief that drinking will lead to negative consequences.

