### Implications of the Study and Suggestions for Future Studies

As previous studies have revealed that seeking alcohol treatment is unpopular in Japan [3], computer-delivered interventions will play an important role for reducing alcohol consumption. To our knowledge this is the first study to examine the efficacy of an internet intervention with personalized normative feedback among Japanese problem drinkers. The authors argue that a Web-based screening and brief intervention can be useful to implement in various settings such as university or workforce. Since the legal drinking age is 20 in Japan, many university students are at risk of underage drinking and thus alcohol-related problems. This study excluded individuals engaging in underage drinking because of ethical responsibility. However, future studies may examine the efficacy of the intervention among university students by including students engaging in underage drinking. One study reports more than half of the students engaging in underage drinking in Japan [38]. Also, statistics show that in Japan men aged between 40 and 60 have the highest alcohol consumption compared to men in other ages or women [5]. Interventions with personalized normative feedback and psychoeducation can be used as a preventative tool before students or workers develop serious problems.

The literature shows ample evidence that alcohol expectancies are associated with drinking behavior [39]. Examining alcohol expectancies as possible moderators between effects of interventions and drinking behavior can contribute to the literature by applying theoretical understanding of drinking patterns into clinical settings.

Although more smartphone-delivered interventions have been used in recent approaches, the present study utilized a laptop or desktop computer. Users are likely in a less distracted environment when sitting in front of a laptop or desktop. Also, users can check the report from the intervention easily with a wider screen. However, future studies may develop a brief intervention using a mobile device and take advantage of its supporting functions.

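### Separate moderator models for alcohol expectancies and AUDIT level cannot tell moderation by belief from moderation by drinking severity, which the expectancy hypothesis requires

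*Protocol article*

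**What the plan says.** Statistical Analyses in the protocol article fixes the moderator strategy: "alcohol expectancies and levels of AUDIT will be separately added into the model". The next sentence keeps the two apart: "Interactions of alcohol expectancies or AUDIT with condition, time, and condition × time (multiplying the two) will be analyzed". Under Measures, AUDIT enters as three categories (hazardous, harmful, dependent), and expectancies have positive and negative aspects.

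Three other statements bear on this choice.

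- **Expectancies and drinking are linked.** Personalized Normative Feedback: "Alcohol expectancies are associated with frequency and quantity of alcohol consumption". The implications section repeats that "alcohol expectancies are associated with drinking behavior".
- **Severity is expected to moderate.** Purpose of This Study: "The reduction of alcohol consumption will be greater among individuals with harmful and hazardous levels of drinking than those at the dependent level of drinking". The Discussion overview repeats this prediction.
- **Expectancy moderation is explained by belief.** Purpose of This Study: "stronger negative or weaker positive beliefs about the effects of drinking will reduce participants’ alcohol consumption", which the article says is "due to participants’ belief that drinking will lead to negative consequences".

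**The concern.** If expectancies are correlated with severity and severity modifies the intervention effect, a model with condition × expectancy but without condition × AUDIT omits a correlated effect modifier. Its expectancy interaction then takes up part of the severity moderation. Randomisation balances the arms but does not remove this, because expectancy level is not randomised.

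This would do little harm if the aim were only to describe which participants respond. The article goes further: it gives a direction for the expectancy effect, explains it by the belief itself, and presents it as a contribution to theory. Separate models cannot support that explanation over the competing one that the article also puts forward.

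The hypothesis is also loosely worded. It says that beliefs will reduce consumption, which is an effect of belief on drinking. Moderation is a difference between arms that varies with belief.

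**Working it through.** The article gives no figure for the moderator analyses, so there is none to reproduce. The check asks how often a null expectancy × condition term is declared significant when only AUDIT level moderates.

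**From the article:** planned sample 600; a cited dropout of 65%, hence 600 × 0.35 = 210 if that rate recurs; significance level 0.05; three AUDIT categories; a smaller effect expected at the dependent level.

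**Assumed, because not given:** correlation r = 0.3 or 0.5 between expectancy and a normal severity scale underlying AUDIT; 20% or 40% at the dependent level; an effect of d = 0.25 or 0.5 SD below that level and 0 at it; 1:1 allocation; two-sided test; residual SD 1; one follow-up in place of the repeated-measures model.

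**Formulas**

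- Spurious slope, in SD of outcome per SD of expectancy: r × d × φ(c). Here φ(c) is the normal density at the dependent cut-off: 0.280 for 20%, 0.386 for 40%.
- Standard error: 2/√N, so 2/√600 = 0.0816 and 2/√210 = 0.138.
- Rejection rate: Φ(z − 1.96) + Φ(−z − 1.96), with z = slope/SE.

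Example: d = 0.5, 20% dependent, r = 0.5. Slope = 0.5 × 0.5 × 0.280 = 0.070. At N = 600, z = 0.070/0.0816 = 0.857, and the rate is Φ(−1.103) + Φ(−2.817) = 0.135 + 0.002 = 13.7%.

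| Effect below vs at dependent level | Dependent | r | Slope | N = 600 | N = 210 |
|---|---|---|---|---|---|
| 0.25 vs 0 | 20% | 0.3 | 0.021 | 5.8% | 5.3% |
| 0.25 vs 0 | 20% | 0.5 | 0.035 | 7.1% | 5.7% |
| 0.25 vs 0 | 40% | 0.3 | 0.029 | 6.5% | 5.5% |
| 0.25 vs 0 | 40% | 0.5 | 0.048 | 9.1% | 6.4% |
| 0.5 vs 0 | 20% | 0.3 | 0.042 | 8.1% | 6.1% |
| 0.5 vs 0 | 20% | 0.5 | 0.070 | 13.7% | 8.0% |
| 0.5 vs 0 | 40% | 0.3 | 0.058 | 10.9% | 7.0% |
| 0.5 vs 0 | 40% | 0.5 | 0.097 | 21.9% | 10.8% |

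**Simulation check** (3,000 trials per setting, AUDIT in three categories). For 0.5 vs 0 at N = 600, the separate model rejected in 8.0% (r = 0.3) and 13.2% (r = 0.5) of trials with 20% dependent, and in 10.4% and 22.2% with 40%. These agree with the table. At r = 0.1 and 20% dependent the rate was 5.5%. A joint model with AUDIT category and its interaction with condition gave a slope of about 0 and rejected in 4.4% to 5.7% of trials across settings.

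**Direction.** At r = −0.3 the simulated slope was −0.044, against 0.042 at r = 0.3. The artefact therefore mimics the hypothesis if positive expectancies rise with severity or negative ones fall with it. It works against the hypothesis if negative expectancies rise with severity.

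**Price of the joint model.** Collinearity multiplies the standard error by 1/√(1 − r²): 1.05 at r = 0.3 and 1.15 at r = 0.5.

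**The case against.** The strongest reply is that the moderator work is called exploratory and that one-at-a-time models validly describe in whom the effect differs. That stands, and it is why the separate models should stay. It does not license the step from description to belief as the reason.

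Second, the key inputs are outside the documents. The article links expectancies to quantity and frequency of drinking, with no coefficient, no sign and no direct statement about AUDIT level. The step to AUDIT is an inference. It is a short one, since the drinking measures are partly drawn from the AUDIT, but entry at a score of 8 or more may weaken the correlation. This also stands, and it limits the size of the claim.

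Third, the larger rates need strong inputs. With 20% dependent, 0.25 vs 0 averages 0.8 × 0.25 = 0.20 SD, which fits a small effect if that is read as 0.2 SD. The 0.5 vs 0 contrast averages 0.40 SD with 20% dependent and 0.30 SD with 40%.

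Fourth, the article treats expectancies as helping to explain drinking, so severity may lie downstream of belief. Adjusting for AUDIT could then remove part of a real expectancy effect. Nor would a joint model prove that belief is the cause. Both points argue against making it the sole basis for reporting on expectancies.

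A reader might infer that severity moderation will show up as the hypothesised expectancy effect. The documents do not support this. In most settings above the false-positive rate is only a few points over 5%, the sign of the correlation is unknown, and for negative beliefs the artefact may hide the effect.

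**Conclusion.** The point holds in a limited form. The article commits to separate moderator models while stating the conditions under which those models cannot separate expectancy from severity, and its hypothesis relies on that separation. The bias is real in principle and a joint model removes it. Its size and direction cannot be settled from the documents.

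Under the assumptions shown, inflation is slight for effects near the protocol's small effect: about 6% to 9% against a nominal 5% at N = 600. It becomes material only with a large contrast by severity and a correlation of 0.5, at about 14% to 22%. With 210 analysed it is about 5% to 11%. These rates ignore the time terms of the planned model. The efficacy comparison between arms is unaffected.

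**What to change.** In Statistical Analyses:

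1. Keep the separate models as planned.
2. Add, as a supplementary analysis for each outcome, one joint model with AUDIT level (the three categories under Measures), positive expectancy and negative expectancy, each with its interactions with condition, time and condition × time.
3. State that an expectancy interaction will be attributed to beliefs rather than drinking severity only if it persists in the joint model, and will otherwise be reported as descriptive.

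In Purpose of This Study, reword the expectancy hypothesis as a between-arm difference in drinking that varies with baseline expectancy.

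The cost is one more model per outcome, on data already being collected, and a few sentences of text. Standard errors for the moderator terms would be roughly 5% to 15% wider at correlations of 0.3 to 0.5. Correlation between the two expectancy aspects, which the article does not give, could add to that.
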